#### Recruitment and sample size

2.2.1

Participants for the evaluation study will be recruited from three consecutive INSIGHT cohorts (2025/2026, 2026/2027, and 2027/2028) Participation in the educational program is independent of participation in the evaluation study. As enrollment in INSIGHT is limited to 25 participants per cohort a maximum sample size of 75 participants can be achieved and no sample size calculation was conducted. Inclusion criteria for the evaluation study include a minimum age of 18 years, fluent command of the German language, and enrollment in INSIGHT. The study’s objectives and relevant information will be provided during the initial lecture of the program, which will take place during the online launch event. During this event, informed consent will be obtained and T0 data collection conducted.

Admission criteria for INSIGHT comprise completion of an academic degree in a health profession or a completed vocational training in a health profession with a minimum of 2 years of professional experience. In addition, a professional connection to oncology is required.

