#### Study design and data collection

2.2.2

The evaluation study is designed as a longitudinal, prospective, single-arm, non-controlled, non-randomized observational pre–post study with follow-up. Given the limited sample size resulting from the restricted enrollment of the educational program, an exploratory analytical approach is adopted. Data will be collected at three time points per cohort: baseline (T0) on the introductory day of the program, at program completion (T1), and at a 6-month follow-up after completion (T2).

At T0, during the first event of the educational program, sociodemographic data will be collected using a standardized questionnaire to characterize the study population. Collected variables include age (categorized), gender, and stratified professional experience. Healthcare profession and professional role within the workplace (e.g., junior or senior physician) will also be assessed. Data collection will be conducted using the online platform SoSci Survey (version 3.8.00) and during the individual courses as well as T0, T1, and T2 a specific timeframe is reserved for the participation in the questionnaires. To support complete data entry, reminder prompts for unanswered items are integrated into the online questionnaire platform.

As an interprofessional educational program focusing on interprofessional counseling in integrative oncology, the primary objective of the evaluation is to examine interprofessional parameters as well as changes in self-perception on professional knowledge and competence on CIH, as detailed below. Given that the curriculum is interprofessional in both its mode of delivery and its intended application, questionnaires addressing interprofessional dimensions constitute the fundamental component of the evaluation approach.

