#### Data analysis

2.2.3

Sociodemographic variables, individual course evaluation and self-perception on professional knowledge and competence on CIH will be analyzed descriptively. Scores obtained from the applied instruments (UWE-IP, ISVS 9A/9B, and EPIS-G) will be compared across the three measurement time points within the same sample. Primary analyses will be descriptive and will include measures of central tendency (means, medians), measures of dispersion, and graphical visualization of temporal trends.

The distributional properties of the data will be examined using the Shapiro–Wilk test in conjunction with visual inspection of Q–Q plots. Exploratory within-subject comparisons across time points (T0, T1, and T2) will be conducted to assess potential changes in scores over time. For normally distributed data, repeated-measures analysis of variance (ANOVA) will be applied, whereas the Friedman test will be used for non-normally distributed data. Given the limited sample size, all inferential analyses will be interpreted in an exploratory manner. Where notable differences are observed, *post hoc* analyses (e.g., pairwise Wilcoxon signed-rank tests with Bonferroni correction) may be performed to further describe changes between specific time points.

Attrition between T0, T1, and follow-up (T2) will be reported using flow diagrams and descriptive statistics (e.g., number and proportion of participants at each time point, reasons for drop-out where available). For within-subject analyses of change over time, only participants with data at the relevant time points will be included. Comparisons of key baseline characteristics between completers and non-completers will be considered to explore potential attrition bias. Missing data will be handled using a complete case approach for analyses of within-subject change over time. No imputation across time points or at the participant level is planned, given the exploratory design and limited sample size. At the item level, person-mean imputation within a scale will be considered if missing responses do not exceed a predefined threshold and the extent and patterns of missing data will be reported descriptively.

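### The three-wave complete-case ANOVA or Friedman test drops anyone missing one wave; a mixed model would use the partial records at little cost

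*Protocol article*

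**What the plan says.** All references are to the protocol article.

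- **Waves (section 2.2.2).** "Data will be collected at three time points per cohort": baseline, the end of the programme, and six months after that.
- **Sample size (section 2.2.1).** "As enrollment in INSIGHT is limited to 25 participants per cohort a maximum sample size of 75 participants can be achieved". The article says that this ceiling does not come from a power or precision calculation.
- **Test (section 2.2.3).** For normally distributed scores, "repeated-measures analysis of variance (ANOVA) will be applied, whereas the Friedman test will be used for non-normally distributed data".
- **Missing data (section 2.2.3).** "Missing data will be handled using a complete case approach for analyses of within-subject change over time". Also: "No imputation across time points or at the participant level is planned, given the exploratory design and limited sample size". Analyses of change take only people who have data at whichever time points are relevant to that analysis.
- **Around it (section 2.2.3).** The primary analysis is descriptive and inferential results are to be read as exploratory. Pairwise Wilcoxon tests with Bonferroni correction are optional. Attrition is to be reported by flow diagram, and a comparison of completers with non-completers on baseline characteristics will be considered.

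**The concern.** Classical repeated-measures ANOVA and the Friedman test work on a rectangular table of people by waves. Under the complete-case rule, someone with T0 and T1 but no T2 contributes nothing to the omnibus comparison, although two of their three measurements are in hand.

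Two things are at stake. The first is precision, in a study whose ceiling cannot be raised. The second is bias: the three-wave estimates describe those who answered every time, and if answering depends on earlier scores, that group's change differs from the whole cohort's. The completer comparison, if done, could reveal such a difference at baseline but would not correct the estimates.

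**Working it through.** **Inputs from the article.** Three cohorts of 25 and three waves. The stated ceiling reproduces: 3 × 25 = 75. The article gives no attrition rate, SD, correlation or expected change, so every other input below is an assumption.

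**Step 1: precision.** If a fraction c of participants completes all waves, the omnibus test uses 75c people. The standard error (SE) of a mean change grows by 1/√c relative to all 75.

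| c | People used | SE factor |
|---|---|---|
| 0.9 | 67.5 | 1.05 |
| 0.8 | 60 | 1.12 |
| 0.7 | 52.5 | 1.20 |
| 0.6 | 45 | 1.29 |

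This is the cost against full data. A mixed model recovers only part of it (step 2).

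**Step 2: simulation.** The set-up was N = 75, 800 replicates per scenario, trivariate normal scores with SD 1, equal correlations of 0.5 or 0.7, and true changes of 0.50 SD (T0–T1) and 0.40 SD (T0–T2). Losses were 0%, 10% or 15% before T1 and a further 20% or 30% before T2. Drop-out was either purely random or more likely for low previous scores (log-odds 0.7 or 1.0 per SD). Complete cases were compared with maximum likelihood (ML) with unstructured mean and covariance, which is the likelihood analogue of the proposed mixed model. With empirical SEs up to about 0.155, Monte Carlo error is at most about 0.155/√800 = 0.005.

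*Random drop-out, correlation 0.5.* There is no bias. Empirical SEs:

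| Loss before T1 / T2 | T0–T1 complete case | T0–T1 ML | T0–T2 complete case | T0–T2 ML |
|---|---|---|---|---|
| 0% / 30% | 0.133 | 0.114 | 0.139 | 0.134 |
| 15% / 30% | 0.155 | 0.122 | 0.150 | 0.138 |

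The gain is mainly in T0–T1 (0.133/0.114 = 1.17 in the first row). For T0–T2 it is small (0.139/0.134 = 1.04), because a missing T2 can be only partly recovered from earlier scores.

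*Score-dependent drop-out.* Mean estimates over both correlations and both slopes:

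| Estimate (true value) | Scenarios | Complete case | ML |
|---|---|---|---|
| T0–T1 (0.50) | T2 loss only | 0.56 to 0.63 | 0.50 |
| T0–T1 (0.50) | loss at both steps | 0.52 to 0.56 | 0.50 to 0.51 |
| T0–T2 (0.40) | T2 loss only | 0.39 to 0.41 | 0.39 to 0.41 |
| T0–T2 (0.40) | loss at both steps | 0.35 to 0.38 | 0.40 to 0.41 |

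Complete-case bias in T0–T1 is therefore about +0.02 to +0.12 SD. In T0–T2 it is near zero or negative, down to about −0.05 SD.

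**Step 3: available T0–T1 pairs.** If a pairwise test uses everyone with T0 and T1, the estimate is 0.50 when only T2 is lost, the same as ML. When T1 non-response depends on T0, pairs give 0.44 to 0.48 against 0.50.

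**Step 4: a mechanism that does not favour ML.** With N = 60, correlation 0.6 and T2 loss depending on a person's stable underlying level (log-odds 1 per SD), the T0–T2 change is 0.40 by complete cases and about 0.46 by ML, against a true 0.40. With loss depending on the T2 score itself, both are off: 0.50 and 0.55.

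**The case against.** The strongest reply is that the rule about relevant time points, read naturally, lets the pairwise T0–T1 comparison use every T0–T1 pair. A reader might infer that T2 drop-out must distort the immediate gain. The text does not support that for the pairwise test, and step 3 shows no such bias. What stands against the plan is narrower: the pairwise tests are optional, the omnibus test still needs three waves, and T1 non-response that depends on T0 biases even the pairs.

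Four further inferences are tempting and should not be made:

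- **That T2 has no protected time.** Section 2.2.2 reserves a period for the questionnaires at T2 as well as at T0 and T1.
- **That people who leave the programme early are excluded by design.** T1 and T2 are defined for each cohort, and nothing makes personal completion a condition for being surveyed.
- **That the small sample is the stated reason for complete cases.** It is given, with the exploratory design, as the reason for not imputing. A mixed model needs no imputation, so that reason does not count against it.
- **That missing at random is the weaker assumption.** Step 4 shows a case where complete-case change is unbiased and ML is not.

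The other side is also right that the primary analysis is descriptive, inference is exploratory, attrition is to be reported, and a Gaussian model does not by itself replace a rank test for bounded Likert scales.

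**Conclusion.** The point holds in limited form. The three-wave tests on complete cases discard partial records in a study of at most 75. The cost is a standard error about 1.05 to 1.29 times the full-data value at an assumed 10% to 40% incomplete. There is also possible bias when drop-out depends on earlier observed scores: about +0.02 to +0.12 SD for T0–T1 in the assumed scenarios, with T0–T2 unaffected or biased downwards. The direction depends on who leaves; with random drop-out only precision is lost. These sizes rest on assumed attrition, correlations and drop-out mechanisms, none of which the article gives.

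The plan is disclosed and internally consistent. This is a worthwhile, low-cost improvement to an exploratory analysis, and no power or sample-size claim depends on it.

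**What to change.** In section 2.2.3, for each scale:

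1. Fit a linear mixed model by REML with time (T0, T1, T2) and cohort as fixed effects and an unstructured within-person covariance, including every participant with at least one measurement.
2. Use a small-sample degrees-of-freedom correction, and bootstrap or robust inference where scores are clearly non-normal.
3. Report model-estimated T0–T1 and T0–T2 changes with confidence intervals.
4. Keep the planned complete-case ANOVA or Friedman test as a sensitivity analysis. State that pairwise comparisons use all participants with both waves, if that is the intention.

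The cost is a change of wording and standard software, with no extra data. The last cohort is 2027/2028, so the change can be made before the final analysis. The downside is reliance on missing at random. Because this and the complete-case assumption fail in different circumstances, reporting both analyses is informative, and a material difference between them should be discussed.

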## Ethical considerations and dissemination

3

Prior to participation, study-specific information regarding study procedures, data protection, and the right to withdraw will be provided, and written informed consent will be obtained from all participants. Participation is voluntary, and participants may withdraw from the study at any time without providing a reason. Pseudonymized data may be deleted upon request by referencing the individual pseudonym.

Data collection will be conducted using the online platform SoSci Survey (version 3.8.00). All data will be stored on secure servers of the University Hospital of Tübingen. The study will be conducted in accordance with the Declaration of Helsinki as well as applicable European and German national regulations. Ethical approval was obtained from the Ethics Committee of the Medical Faculty of the University of Tübingen (Approval No. 2025-0617-BO).

In addition to feedback provided to the study population, anonymized study results will be disseminated through peer-reviewed scientific journals and presentations at scientific conferences.

## Discussion

4

The development of the INSIGHT curriculum responds to a well-documented gap between the high prevalence of CIH use among oncology patients and the limited training of healthcare professionals in evidence-based counseling targeting integrative oncology (9). International data indicate that approximately 40–80% of oncological patients use or consider CIH interventions, depending on tumor entity and study design (2). Despite this widespread use, many clinicians in Germany as well as in other countries report insufficient knowledge and low confidence in advising patients on the potential benefits, risks, and interactions of integrative approaches (9, 37). Professional organizations and guidelines such as the American Society of Clinical Oncology or the German national guideline on complementary medicine in oncology emphasize the importance of structured education and interdisciplinary collaboration to ensure safe, patient-centered integrative oncology care (3, 38).

The INSIGHT program contributes to this field by integrating evidence-based CIH knowledge with interprofessional communication training in a blended-learning format. Interprofessional education may be a key strategy to improve collaboration and quality of care in complex clinical settings such as oncology (39, 40). Similarly, blended learning has shown effectiveness in continuing medical education by improving learner engagement, the autonomy of learners, satisfaction and knowledge retention compared with traditional teaching formats (41, 42). Combining these approaches may therefore be particularly suitable for integrative oncology counseling, which requires both critical appraisal of heterogeneous evidence, evaluating the inclusion of consensus-based interventions with lacking evidence in counseling and collaborative decision-making across professional boundaries. The World Health Organization’s Framework for Action on Interprofessional Education and Collaborative Practice positions interprofessional education as a key strategy to build a “collaborative practice-ready” health workforce and strengthen health systems through effective teamwork across various health professions (43). The INSIGHT program contributes to this goal by operationalizing this framework, integrating evidence-based CIH content with interprofessional communication training in a blended-learning format.

The planned prospective pre-post evaluation using validated interprofessional instruments allows an initial assessment of changes in self-perceived competencies and attitudes. However, the non-controlled design limits causal inference, and reliance on self-report measures may introduce social desirability bias or response-shift effects. Long-term follow-up is also needed to determine whether educational gains translate into sustained practice change and improved interprofessional collaboration. Performance-based assessments or observational examinations, such as objective structured clinical examinations, may offer a more objective evaluation option increasing the validity of the findings. However, after intensive discussion within the research team, the decision was made not to implement such assessments due to the substantial resources required for their administration and execution. Participants travel from across Germany, so on-site time is deliberately kept to a minimum to support compatibility with work and everyday life, with a clear focus on the acquisition of practical skills. Therefore, participant-reported assessments were chosen for the evaluation of the educational program. While the curriculum is explicitly designed for direct transfer into professional practice and to equip participants with competencies for interprofessional CIH counseling, the present evaluation focuses on self-reported competence and interprofessional outcomes and does not include performance-based assessments of counseling in real-world clinical encounters, which limits the extent to which actual practice change can be investigated.

If positively evaluated, the INSIGHT curriculum could serve as a scalable model for integrating evidence-based CIH education into oncology training programs and cancer center structures. Such initiatives may contribute to safer integrative care, improved communication about CIH use, and more informed shared decision-making, which are increasingly recognized as essential components of high-quality oncology care.
